### **Data and Safety Monitoring Plan**

#### **1. Summary of the Protocol**

The proposed study is a hybrid Type 2 implementation-effectiveness trial in which 8 counties will be cluster-randomized to a stepped-wedge start date for receiving the LHS intervention to improve the substance use care cascade for youth involved in the juvenile justice system. Study participants include juvenile justice agency and community mental health center staff, as well as justice-involved youth and their parents/guardians.

As detailed in the Protection of Human Subjects section, study participants of all types face minimal risks associated with study participation. Most risks would be associated with potential loss of confidentiality or minor psychological discomfort.

#### **2. Roles and Responsibilities**

[name] (PI) will be responsible for monitoring the safety of the study, executing the DSMP, and complying with reporting requirements. These efforts will be co-led by [name]. [name] will provide a summary of the DSMP report to NIDA each year as part of the progress report. The DSMP report will include the participants' demographic characteristics, expected versus actual recruitment rates, any quality assurance for issues that occurred during the past year, a summary of adverse events, and any actions or changes with respect to the protocol. The DSMP report to NIDA will include the results of any data analysis.

#### **3. ADAPT Safety**

ADAPT safety monitoring will be conducted by Drs. [name] and [name] throughout the study in compliance with the following requirements of the Indiana University IRB's continuing review process:

- 1) Tracking of subject accrual (enrollment, drop-outs, demographics)
- 2) Timely and appropriate reporting of informed consent process deficiencies, protocol deviations, privacy breaches, conflicts of interest, and/or changes in personnel

3) Ongoing monitoring and appropriate reporting of adverse event activity

- a. Internal: i) frequency of unexpected, related or possibly related, and serious or more prevalent than expected adverse events; ii) frequency of internal deaths occurring during the study or within 30 days of study termination, even if expected or unrelated
- b. External: frequency of unexpected, related or possibly related, and serious adverse events

4) Interim assessment of risk/benefit relationship in reference to adverse event occurrences, preliminary observations, and emerging information

5) Timely and appropriate IRB submission of safety-related documents such as audit reports, sponsor progress reports, and other materials or communications that might impact the safe conduct of this study

6) Active cooperation with the IRB and other applicable entities in the event of a random or for-cause internal or external audit

4. Interim Analysis and Stopping Rules

Formal interim analysis is planned for this study at 18-month point. The PI may prematurely terminate the study if deemed necessary, although this is not expected due to the minimal risks involved in conducting the study.

5. Monitoring and Reporting

- 1) Identification. Potential risks identified for participants will be listed in the IRB-approved informed consent document. Additional unknown risks might occur and, if so, will be identified through diligent investigator monitoring throughout the conduct of this study.
- 2) Detection. During the informed consent process, participants will be advised of the potential risks of participation as identified in the IRB-approved informed consent document. Participants will be advised during the informed consent process that they should promptly inform the investigators of any concerns regarding adverse events related to participation in the study. Safety parameters will be followed by the PI as outlined above.
- 3) Grading. Adverse events will be assessed and graded according to the IU IRB Adverse Event Reporting Policy:
  - a. Expected/Anticipated Adverse Event: Identified in nature, severity, or frequency in the current protocol, informed consent, investigator brochure, or with other current risk information.
  - b. Unexpected/Unanticipated Adverse Event: Not identified in nature, severity, or frequency in the current protocol, informed consent, investigator brochure, or with other current risk information.
  - c. More Prevalent: Occurs more frequently than anticipated or at a higher prevalence than expected.
- 4) Attribution. Adverse events will be attributed to study participation according to the IU IRB Adverse Event Reporting Policy:
  - a. Unrelated: There is not a reasonable possibility that the adverse event may have been caused by participation in the study.
  - b. Possibly Related: The adverse event may have been caused by participation in the study; however, there is insufficient information to determine the likelihood of this possibility.
  - c. Related: There is a reasonable possibility that the adverse event may have been caused by participation in the study.

- d. Seriousness: Results in death, is life threatening, requires inpatient hospitalization or prolongs existing hospitalization, results in persistent or significant disability/incapacity, or any other event that may jeopardize the participant's health and may require medical or surgical intervention to prevent one of the other outcomes listed in this definition.
- 5) Reporting. Adverse events experienced by participants will be reported using the IRB's password protected on-line adverse event reporting system, in keeping with the IU IRB Adverse Event Reporting Policy as follows:
- a. Internal Adverse Events. An internal adverse event is reportable if the occurrence meets all three of these conditions: 1) is unexpected, 2) is related or possibly related to participation in the research, and 3) is serious or places participants or others at greater risk of physical or psychological harm than was previously known or recognized. Internal adverse events are not reportable under these conditions: 1) expected and not more prevalent than expected, whether related or unrelated, and 2) unexpected and unrelated, regardless of seriousness, aside from death.
- b. Internal Deaths. All internal deaths occurring during the conduct of the study or 30 days post-termination from protocol are required to be reported as adverse events even if they are expected or unrelated.
- c. IRB Reporting Schedule for Adverse Events. For any unexpected and related or possibly related, serious or more prevalent event occurring during a research study, a report must be made through the IU online reporting system as soon as possible but no later than 10 working days after the investigator first learns of the event. All other (expected adverse events) are reported as aggregate data at the time of IRB continuing review.
- d. Report of Changes or Amendments to the Protocol. The annual DSMP report will describe any minor actions or changes with respect to the protocol. In the unlikely event that major changes are required, the Principal Investigator will discuss the needed changes with the NIDA Program Official first, reach a consensus agreement on the changes with the Program Official, and then provide a written description of the changes to NIDA.

## 6. Data and Safety Monitoring Board

NIDA will establish a Data and Safety Monitoring Board (DSMB) that will be responsible for safeguarding the interests of all Justice Community Opioid Innovation Network (JCOIN) participants. The DSMB will be comprised of external experts who will be responsible for monitoring study data relevant to bioethics and the safety of the study participants and impacts on study operations and procedures. JCOIN contact PIs will be responsible for providing the DSMB timely information about their projects as requested, including reporting to the DSMB at least annually. The DSMB will make recommendations to NIDA with respect to: 1) Participant safety, confidentiality, and informed consent, including notification of adverse events; 2) participant burden; and 3) impact of proposed ancillary studies and sub-studies on participant burden and overall achievement of the main study goals.

Protocol: ADAPT

PI: [name]

577

## 6 Clinical Performance Sites

Eight counties, i.e., JJ system jurisdictions, across Indiana participated in ADAPT. A local CMHC per site also participated. Names of the counties and CMHCs are withheld from publication.

### *LHS Alliances by Site*

LHS alliance teams will be composed of existing JDAI local data teams. The local JDAI data teams consist of JJ personnel and community members. The goals of the data teams are to assess local data to determine youth risk level and to improve outcomes among YJJ. LHS alliance teams will utilize these teams, along with additional team members from the local CMHC, to conduct continuous quality improvement cycles.

### *State Advisory Board*

The ADAPT State Advisory Board will consist of delegates from state agencies, academic consultants, local practitioners, and youth and parent stakeholders identified through local IJDAI partners. The purpose of the State Advisory Board will be to 1) evaluate the strengths and weaknesses of ADAPT; 2) recommend state and local policies to enhance impact; 3) disseminate study results, and 4) explore sustainability. The Advisory Board will receive an annual report on ADAPT progress and meet twice yearly with [name]. ADAPT co-Is, [name] and [name], will convene a policy gap workgroup of board members, on an as-needed basis to conduct policy analyses relevant to ADAPT.

## 7 Study Design

### *Learning Health System*

A central goal of this project is to build a collaborative alliance between JJ and CMHC agencies. The reason to do so is to improve substance use treatment referral and substance use treatment outcomes for YJJ. An LHS includes continuous quality improvement and the development of professional teams to develop interventions and evaluate the outcome. We will use already established implementation methodology ("Agile Implementation") for the LHS intervention. Agile Implementation utilizes an 8-step process to effect change. We will adapt the AI training for the current setting. In order to make the continuous improvement cycles effective, our research team will link local juvenile justice and community mental health center data for each site. We will do so on a quarterly basis and the data can be used during local committee meetings. Our research team has extensive experience conducting deterministic and probabilistic linking and cross-sectional data linking of justice-involved youth to CMHC data of this size will be straightforward. We will also work with the data programmer affiliated with the Juvenile Detention Alternatives Initiative (JDAI), [name], to develop these tables for informing interventions. He has done this work at the local and state level for many years.

### *Substance Use Risk Screening*

Based on research and our pilot data, substance use risk screening will need to be implemented universally to assess the extent of each community's need for connection to substance use treatment services.

### *Assessing Outcomes*

*Implementation outcomes.* This is a hybrid Type II effectiveness implementation trial. Thus, we are interested in the implementation of the LHS intervention. We will assess implementation with self-report surveys, qualitative interviews, and focus groups. We will also include the Stages of Implementation Completion (SIC) measure, an 8-staged observation-based assessment tool created as part of a large-scale randomized implementation trial comparing two implementation processes. The SIC stages - which we will apply throughout the study period to measure implementation outcomes - range from: Engagement with the academic team to achievement of practitioner Competency and map onto three well-accepted phases of implementation (Pre-Implementation (i.e., exploration and planning), Implementation, Sustainability). The SIC has demonstrated valid and reliable measurement of implementation activities, specifically the proportion and duration of implementation activity completion. Lastly, we will complete three sets of qualitative and focus group interviews. By utilizing a mixed method approach, will be triangulate results and gather a more nuanced picture of implementation issues.

*Substance use care cascade.* A primary outcome of interest is the SU care cascade (Cascade). The Cascade includes a spectrum of outcomes. At any point in the Cascade, a young person can “drop out.” The earliest stage of the Cascade occurs within the juvenile justice system: identification of treatment need (i.e., screening and assessment) and referral to services. The latter end of the Cascade occurs within the CMHC: treatment initiation, engagement, and completion. We are interested in determining whether the LHS intervention is effective in improving the Cascade. We will evaluate this outcome utilizing administrative data on the entire population of YJJ across all 8 sites. We will gather Cascade data from the local CMHCs as well as Department of Child Services (DCS) and Medicaid. The reason for gathering data from DCS and Medicaid is they both provide funds for outpatient services. Thus, if a young person receives substance use services outside of the local CMHC, we will be able to gather at least a portion of it from these data sources. We may find that the effectiveness of LHS is improved for young people seeking services outside of the CMHC. With that said, we have collaborated with the largest CMHC of each jurisdiction and most jurisdictions only have one CMHC located in their county. We will also be able to control for time spent outside of the community by controlling for commitments to Department of Corrections (gathered from the juvenile justice data set) and residential placement (gathered from DCS and Medicaid).

*Criminal recidivism.* We will also assess whether the LHS intervention is effective in limiting recidivism. We will utilize the existing juvenile justice information system to assess recidivism. We will focus on the prediction of new criminal charges rather than charges associated with previous criminal behavior (e.g., technical violation, probation violation and warrants).

*Opioid-related outcomes.* By linking with data collected through the Regenstrief Institute Addictions Data Commons, we will be able to assess a variety of outcomes. This includes hospital and Emergency Department visits for opioid use disorders (OUD) as well as emergency medical service runs due to opioid use. These data elements are now incorporated within the Addiction Data Commons.

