### 2 Study Population Characteristics

#### Eligibility Criteria

We describe participant eligibility for three distinct subgroups of participants:

1. Juvenile Justice (JJ) and Community Mental Health Center (CHMC) system personnel (i.e., administrators and staff) and members of the ADAPT State Advisory Board (Board; community leaders and stakeholders); study of implementation outcomes: System personnel and Board members are eligible for study enrollment if they 1) are employed by a JJ or CMHC agency within a participating county (i.e., research performance site) during the study period OR serve on the Board; and 2) are age 18 years or older.

2. Youth involved in the juvenile justice system (YJJ), administrative records sample.

a. YJJ, total administrative records sample: YJJ are eligible for inclusion in this sample if they are 1) arrested or otherwise referred to the juvenile justice system within a participating county (i.e., research performance site) during a 10-year period, including during 5 years before the study period and during the 5-year study period; and 2) ages 11-22 years old, inclusive, at the time of their first arrest/referral within the 10-yr period of data collection.

b. YJJ, Learning Health System (LHS) working record sample: YJJ are eligible for inclusion in this sample if they are 1) arrested or otherwise referred to the juvenile justice system within a research performance site county that is actively receiving the LHS intervention (see timeline); and 2) ages 11-22 years old, inclusive, at the time of their first arrest/referral during the LHS intervention period (see timeline). Note that the sample of YJJ included in the LHS records sample is a subset of YJJ included in the total administrative records sample. Data related to these youth will be reviewed on a quarterly basis by the LHS alliances.

3. YJJ and Parent/Guardian Dyads; qualitative interviews:

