### **Inclusion of Children / Inclusion Across the Lifespan**

Children ages 11 up to age 18 are a primary focus of the proposed study. The Indiana juvenile justice system has jurisdiction over cases in which offenses were committed by a child before the age of 18, and juvenile justice records may include information regarding youth in the system up until age 23. While there is no formal minimum age of juvenile justice system jurisdiction, cases involving children younger than age 11 are extremely rare. As a practical matter, children younger than 11 years old will be excluded from study enrollment; exclusion of younger children will contribute to meaningful assessment of study outcomes, as the proposed age range is representative of the YJJ population in Indiana. We will collect administrative health and justice data regarding sampled YJJ to assess the effectiveness of an intervention (the LHS) on the substance use services care cascade for YJJ, as well as on public health and safety outcomes.

Our sample of CMHC and JJ personnel, along with Board members, will include adult participants only (ages 18 years old and older) without any maximum age restriction. This age range is justified because it is also a requirement of CMHC and JJ agency employment or Board participation to be age 18 or older.

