The overarching design of the proposed research is a cluster-randomized stepped-wedge testing the effectiveness of the LHS intervention across 8 Indiana counties (i.e., clinical research performance sites). Outcomes of interest include improvements in the substance use treatment cascade (Cascade) outcomes (i.e., treatment need identification, referral to treatment, and treatment initiation and engagement). We are also interested in public health and safety outcomes, including opioid-related outcomes (e.g., overdose rates, opioid-related ED utilization) and criminal recidivism (i.e., rearrests). Administrative health and justice system data will be collected to measure outcomes for this sample. YJJ will be included in the total administrative sample if they are arrested or otherwise referred to the juvenile justice system in one of the participating 8 counties during a 10-year period: 5 years pre-study period plus the 5-year study period. We conservatively estimate that approximately 3,190 YJJ will be eligible for inclusion in the study. This is a conservative estimate for several reasons, explained in greater detail in the power section for Aim 4. Briefly, it is conservative for the following reasons. First, we anticipate 2,170 adolescents will be arrested per year from the 8 counties (6,510 over 36 months including 30 months of intervention plus 6 prior months during the control or baseline condition for the step wedge design). Second, we will use administrative data from 5 years (not just 6 months) for the baseline period in the analysis; however, to be conservative, our step wedge power calculation assumes only 6 months of prior baseline administrative data (i.e., 36 months of primary administrative measurement). Third, we conservatively assume that 30% of youth will be placed out of the home (DOC and residential placement) or will migrate out of the community, resulting in an estimated 70% of 2,170 (i.e., 1,519) adolescent arrestees per year from the 8 counties (4,557 total over 36 months of primary administrative measurement). Fourth, we estimate that 30% of the 4,557 arrests will represent repeated arrests from the same youth, yielding an estimated 3,190 unique youth (i.e., 70% of 4,557) over 36 months. All data, including multiple arrests for the same youth, will be captured in the poisson model for Aim 4 analysis to decrease selection bias, increase power, and increase external validity and generalizability; however, to be conservative, we assumed in our power analysis that only 1 arrest per youth would be available (i.e., 3,190 unique youth).

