#### *YJJ – Administrative Records*

Research materials include electronic administrative health and justice system records from multiple sources listed below. Identifying information, including participant name, SSN, address, MRN, etc., will be used to link available data across systems for each YJJ sampled. The linkage process uses a combination of deterministic and probabilistic algorithms to identify records of the same individual across data sources. The ADAPT research team will then de-identify linked datasets for analysis. Participants will be linked to their data only via unique study ID generated by the research team. The linkage between subject identifying information and study ID will be permanently destroyed at completion of the study. Access to files containing identifiable subject information is limited to a list of investigators maintained in the project's approved IRB protocol.

- *Justice system involvement data:* We are able to capture all sample youth interactions within juvenile justice agencies from each county. Variables will include, but are not limited to, offense type, date of arrest/referrals, criminal history, length of detention stays or incarceration, case disposition requirements and recommendations, and urine drug screen results.
- *Health data:* We will collect any CMHC records (e.g., visit data, service referrals) available for all YJJ in intervention sites. We recognize that youth may receive services in locations other than the local CMHC. Thus, we will also collect administrative health data from the following sources:
  - CMHC records. We will access visit data through the LHS intervention. We will also gather initial screening data, including mental and substance use screening measures used by CMHCs. These measures will be self- or parent-report and vary based on CMHC protocols.
  - Medicaid insurance claims. We will access all behavioral health carve-out data across the entire 10-year data collection period, including services provided by the Medicaid Rehabilitation Option and health insurance coverage for youth in foster care. Medicaid claims data include all pharmacy, outpatient, emergency department, and inpatient encounters (which can be categorized by service type: mental health, substance use, physical health, reproductive health, trauma care, etc.). We will calculate visits based on ICD-10 codes, consistent with previous work.

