|---------|----------------------------|-----------------------------------------------------------------------------|-------------------------------------------------------------------------------------------------------------------------------------------------------------------------------------------------------------------------------------------------------------------------------|
|         |                            | admin sample;
42 months LHS
intervention
sample                    | the LHS intervention on the Cascade (i.e., substance use treatment need identification, referral to services, initiation of services, and engagement in services).                                                                                                            |
| Primary | Criminal
recidivism     | 10 years, total
admin sample;
42 months LHS
intervention
sample | We will evaluate criminal recidivism across the 10-year administrative data collection period. We will assess if Cascade improvement is associated with decreased criminal recidivism. We will also assess if there are intervention-specific effects on criminal recidivism. |
| Primary | Opioid-related
outcomes | 10 years, total
admin sample;
42 months LHS
intervention
sample | We will use administrative data to assess opioid-related outcomes. We will assess if Cascade improvement is associated with decreased opioid-related outcomes. We will also assess if there are intervention-specific effects on opioid-related outcomes.                     |

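### Recidivism, a primary outcome over 10 years, is read only from juvenile records, which cannot show a new offence committed at 18 or over, although youth may enter up to age 22

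*Protocol*

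**What the plan says.** Protocol, Outcome Measures, lists criminal recidivism as a primary outcome: "We will evaluate criminal recidivism across the 10-year administrative data collection period". The same entry plans to examine whether Cascade improvement goes with lower recidivism, and whether there are intervention-specific effects.

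Protocol section 7, Assessing Outcomes, gives the source: "We will utilize the existing juvenile justice information system to assess recidivism". It gives the event as well: "We will focus on the prediction of new criminal charges rather than charges associated with previous criminal behavior".

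The data description under YJJ – Administrative Records keeps justice data within juvenile agencies: "We are able to capture all sample youth interactions within juvenile justice agencies from each county". No adult arrest or adult court source is listed. Department of Corrections commitments are also taken from the juvenile data set.

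Protocol section 2, Inclusion of Children / Inclusion Across the Lifespan, limits what that system covers: "The Indiana juvenile justice system has jurisdiction over cases in which offenses were committed by a child before the age of 18". It adds that "juvenile justice records may include information regarding youth in the system up until age 23".

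Eligibility Criteria, item 2a, admits youth "ages 11-22 years old, inclusive, at the time of their first arrest/referral within the 10-yr period of data collection".

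Nowhere is recidivism time at risk said to end at 18.

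**The concern.** Each statement is reasonable alone, but together they leave the outcome unobservable for part of the follow-up. After the 18th birthday a new offence falls outside the only source named. A record without recidivism then means that none could be seen, not that none occurred. For anyone entering at 18 to 22 this applies from the first day.

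Three things are at stake. The recidivism rate is understated if post-18 time is counted. The outcome does not mean what its name says over a 10-year horizon. And because a followed cohort grows older with calendar time, while the LHS also arrives with calendar time, a comparison that does not adjust for period can mistake ageing out for benefit. The planned association between Cascade improvement and recidivism is open to this if Cascade improves over the same years.

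**Working it through.** **The protocol's own figures.** It gives no figure for observable recidivism follow-up. The nearest count reproduces: 2,170 × 3 years × 0.70 × 0.70 = 3,189.9, stated as 3,190. This does not bear on the point, except that it removes 30% for placement and migration and nothing for ageing out.

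**Bound by entry age (no distribution needed).** For a youth followed a full 10 years, the share of time at 18 or over is 1 − (18 − entry age)/10:
- entry at 11: 30%
- entry at 15: 70%
- entry at 17: 90%
- entry at 18 to 22: 100%

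**Share over the cohort (age distribution assumed).** Suppose entry dates are spread evenly over a window of W years and follow-up runs to its end. Mean follow-up is W/2. If ages at first arrest are even over a range ending at 18 and j years wide, mean time before 18 within follow-up is:
- j/2 − j²/(6W) when j ≤ W
- W/2 − W²/(6j) when W ≤ j

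| Ages at first arrest | Mean age | 10-year window | 36-month window |
|---|---|---|---|
| Even, 12–18 (j = 6) | 15.0 | 1 − (3 − 36/60)/5 = 1 − 2.40/5 = 52% | 1 − (1.5 − 9/36)/1.5 = 17% |
| Even, 14–18 (j = 4) | 16.0 | 1 − (2 − 16/60)/5 = 1 − 1.73/5 = 65% | 1 − (1.5 − 9/24)/1.5 = 25% |
| Triangular 11–18, peak 16.8 (simulated) | 15.3 | 55% | 15% |

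For the 42-month window named in Outcome Measures, the two even distributions give 3.5/(3 × 6) = 19% and 3.5/(3 × 4) = 29%. A younger mix, even over 11–18, gives 1 − (3.5 − 49/60)/5 = 46% over 10 years.

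**Effect on the rate.** Assume a constant offending rate before 18 and count post-18 days as event-free. The recorded rate is then 1 − 0.65 = 35% to 1 − 0.52 = 48% of the rate per day under 18 over 10 years, and 75% to 85% of it over 36 months.

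**Effect on the rate ratio.** I fitted a Poisson model with county effects and a log-days offset to expected counts on the protocol's 8-county, 6-period design matrix. There was no true effect, follow-up was open-ended, and the three age distributions above were used.

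| Cohort | Post-18 share, first to last period | Null rate ratio, no period effects | With period effects |
|---|---|---|---|
| No entrants before the 36 months | 0.5%–4% rising to 23%–34% | 0.80–0.87 | 1.00 |
| Five prior years of entrants included | 44%–62% rising to 61%–74% | 0.79–0.80 | 1.00 |

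If each youth is instead followed for a fixed 12 or 24 months, with prior entrants included, the post-18 share is flat across periods (4%–13% or 15%–25%). The null ratio is then 1.00 with or without period effects.

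**The case against.** **Records run to age 23.** The sentence concerns youth already in the system. A late-filed charge for an offence before 18 could appear, but a new offence at 18 or over could not. What stands is that post-18 time is nearly, not strictly, empty.

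**The protocol does not say that post-18 days are counted as event-free.** This stands. The log-days offset in Aim 4 Analyses belongs to a model stated for the Cascade and opioid outcomes. Applying it to recidivism is an inference, although no other recidivism model is given. Ten years is likewise the data period; no follow-up length per youth is stated. The note after the Aim 4 power report does speak of data becoming unavailable as youth leave the system, but it does so to justify the power assumption and defines no time at risk.

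**The trial's test would be protected.** Largely so. Aim 4 relies on standard stepped-wedge methods, which normally include period effects, and the null ratio is then 1.00. A reader might infer that ageing out biases the randomised LHS effect on recidivism. The documents do not support that, since no period-free primary analysis is proposed. A reader might also infer that unequal county ages would bias the contrast even with period effects. No county age difference is documented. Once five prior years of entrants are included, half-year shifts in opposite directions in cohorts 1 and 3 move the null ratio only to 0.996–1.003.

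**Handling of time at risk can be left to the analysis plan.** In general, yes. Here, though, the protocol itself fixes a source, an age range and a time frame that do not fit together.

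**Conclusion.** The point holds for what the outcome can measure. On the protocol's own statements, recidivism at 18 or over is unrecordable apart from late-filed charges, and entrants aged 18 to 22 have essentially no observable recidivism.

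The percentages rest on an assumed age mix, evenly spread entry and follow-up to the end of the data. Shorter fixed follow-up makes them smaller. The null ratios of 0.79 to 0.87 need open-ended counting as well as a comparison without period effects.

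The main harm is to the absolute rate, the meaning of the outcome, and non-randomised readings such as the Cascade–recidivism association. With period effects and similar county age mixes, the randomised rate ratio is essentially unbiased. This should be corrected, but it does not undermine the stepped-wedge test.

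**What to change.** For recidivism only:
- End time at risk, and any offset, at the 18th birthday or the last day in the community, whichever comes first.
- Exclude youth whose index referral is at 18 or over from this outcome.
- Keep 6-month period effects in the model, and in the analysis relating Cascade improvement to recidivism.
- Name the outcome juvenile recidivism in Assessing Outcomes and Outcome Measures.
- Derive the date of turning 18 before date of birth is destroyed. The protocol destroys it once records are linked (YJJ – Administrative Records, destruction of identifiers).

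The cost is one derivation rule and a substantial share of the 10-year person-days. Those days carry almost no recordable new offences, so little information goes with them; a few late-filed charges for offences before 18 may be lost. If the aim is recidivism into adulthood, the alternative is to add an adult criminal record source, which the protocol does not currently list.
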